## Abstract

**Background:**

Accidental awareness during general anesthesia (AAGA) is defined as an unexpected awareness of the patient during general anesthesia. This phenomenon occurs in 1%-2% of high-risk practice patients and can cause physical suffering and psychological after-effects, called posttraumatic stress disorder. In fact, no monitoring techniques are satisfactory enough to effectively prevent AAGA; therefore, new alternatives are needed. Because the first reflex for a patient during an AAGA is to move, but cannot do so because of the neuromuscular blockers, we believe that it is possible to design a brain-computer interface (BCI) based on the detection of movement intention to warn the anesthetist. To do this, we propose to describe and detect the changes in terms of motor cortex oscillations during general anesthesia with propofol, while a median nerve stimulation is performed. We believe that our results could enable the design of a BCI based on median nerve stimulation, which could prevent AAGA.

**Objective:**

To our knowledge, no published studies have investigated the detection of electroencephalographic (EEG) patterns in relation to peripheral nerve stimulation over the sensorimotor cortex during general anesthesia. The main objective of this study is to describe the changes in terms of event-related desynchronization and event-related synchronization modulations, in the EEG signal over the motor cortex during general anesthesia with propofol while a median nerve stimulation is performed.

**Methods:**

STIM-MOTANA is an interventional and prospective study conducted with patients scheduled for surgery under general anesthesia, involving EEG measurements and median nerve stimulation at two different times: (1) when the patient is awake before surgery (2) and under general anesthesia. A total of 30 patients will receive surgery under complete intravenous anesthesia with a target-controlled infusion pump of propofol.

**Results:**

The changes in event-related desynchronization and event-related synchronization during median nerve stimulation according to the various propofol concentrations for 30 patients will be analyzed. In addition, we will apply 4 different offline machine learning algorithms to detect the median nerve stimulation at the cerebral level. Recruitment began in December 2022. Data collection is expected to conclude in June 2024.

**Conclusions:**

STIM-MOTANA will be the first protocol to investigate median nerve stimulation cerebral motor effect during general anesthesia for the detection of intraoperative awareness. Based on strong practical and theoretical scientific reasoning from our previous studies, our innovative median nerve stimulation–based BCI would provide a way to detect intraoperative awareness during general anesthesia.

**Trial Registration:**

Clinicaltrials.gov NCT05272202; https://clinicaltrials.gov/ct2/show/NCT05272202

**International Registered Report Identifier (IRRID):**

PRR1-10.2196/43870

## Introduction

Unexpectedly awakening during surgery is a terrifying experience for patients, who fear it, but also for the medical staff, who are worried that the situation may occur under their supervision [1]. This type of phenomenon is called an accidental awareness during general anesthesia (AAGA) [2]. Although its origin is still debated, the reasons and factors favoring AAGA are being studied. This phenomenon appears if the depth of anesthesia, induced by the concentration of anesthetic used, is not deep enough to compensate for all the surgical stimuli related to the operation in progress. The role of the anesthetist is to succeed in inducing an altered state of consciousness, which is complexly intertwined with analgesia and amnesia. Indeed, if the anesthesia is too light, it may result in recovery of consciousness and volitional movement during the operation, which would be very dangerous for the patient [3]. Conversely, if too much anesthetic agent is given, it increases the depth of anesthesia but may lead to problems such as adverse cardiovascular effects, postoperative delirium, and cognitive impairment, increasing the probability of mortality during surgery [4]. Finally, an anesthetic overdose may also increase the symptoms of postoperative nausea and vomiting and thus delay the patient’s discharge from the hospital [5].

The rate of AAGA in high-risk practices (eg, obstetric, cardiac, and thoracic) varies from 1% to2% [6]. Considering that hundreds of millions of general anesthesia are performed each year worldwide, new solutions to better prevent this phenomenon are needed [7,8]. AAGA can also cause physical pain [2] and lead to psychological sequelae called posttraumatic stress disorder [1-3], which can last for several years and have severe psychological effects leading to suicide [9,10]. From the economic impact perspective, AAGAs generate direct costs because it is one of the top 3 causes of complaints against hospitals (*>*US $43,000 per claim) [2,3,11] and indirect costs from the expenses related to the follow-up and psychological support of the patient who has experienced an AAGA. There are currently 2 procedures to monitor the depth of anesthesia based either on the observation of the clinical features (eg, heart rate, temperature, blood pressure, and movement) or electroencephalographic (EEG) analysis. Unfortunately, the first one does not prevent AAGA during surgery may be because such clinical signs observations remain a very indirect way of monitoring the patients’ cerebral state not always enabling the anesthesiologist to predict an AAGA before it occurs [12]. Although new devices based on frontal EEG activity indexes are already in use, the studies demonstrating the superiority compared to clinical surveillance or end-tidal anesthetic gas [13-16] are not conclusive. Moreover, several studies consent to the use of BIS as it has been shown that the predictive accuracy is decreased when using neuromuscular blockers [1].

The patients’ testimonies show that the first reaction during an AAGA is usually to move to alert the medical staff [2,17]. Unfortunately, during most surgeries, the patient is curarized, which causes neuromuscular block and prevents any movement. Detecting movement intention (MI) is possible by analyzing EEG signals from the motor cortex with a brain-computer interface (BCI). This is based on previous evidence demonstrating that simple MIs are characterized by power spectrum variations (ie, event-related (de)-synchronization called ERD/ERS) in the EEG mu (7-13 Hz) and beta (15-35 Hz) bands over the motor cortex [18] and that electrical stimulation of the median nerve also induces changes in the cortical activity [19,20], which are visible in the EEG signal and which are similar to an MI [21,22]. Interestingly, our preliminary results suggested that when a hand MI coincides with median nerve stimulation (MNS), the ERD/ERS is considerably reduced, and thus the MI can be detected much better by machine learning techniques than an MI without MNS [23-26]. The originality of this BCI paradigm is to exploit this MNS-induced phenomenon to accurately detect the patient’s motor intention during an AAGA. Based on these previous results, we envisage a routine procedure where the anesthetized patient is stimulated by electrical pulses delivered at the median nerve position at the wrist, while a BCI device analyzes the ERD and ERS modulations over the motor cortex to detect the intention of movement of the patient. Our previous clinical trial (MOTANA protocol [23]) also includes a condition with MNS and another with MNS accompanied by MI for 3 concentrations of propofol (0, 0.5 µg/mL, and 1 µg/mL). The preliminary results (n=15) highlighted the advantage of a BCI based on MNS from both a functional and an accuracy point of view. First, MNS intrinsically provides a trigger to know when to analyze the signal. Second, the classification accuracy of an MNS-based BCI appeared to be way better than that of a BCI aiming to discriminate a motor imagination from a resting state. More precisely, an MNS-based BCI detected the MI state 15% more accurately. For several subjects, the use of MNS improves performance by more than 20% compared to a standard method [22,25].

These preliminary results also showed that propofol sedation (at 0.5 µg/mL and 1 µg/mL) has no negative impact on the ability of an MNS-based BCI to detect MI. Concretely, at relatively low concentrations, ERD/ERS patterns are still present in the sensorimotor cortex [26]. From these encouraging results, we intend now to verify that the oscillatory activity generated by the MNS remains present during general anesthesia with higher concentrations of propofol. This is in line with the existing literature, suggesting that the detection of MNS under general anesthesia can be achieved as somatosensory cortex maintains a certain activity confirmed by the presence of evoked potentials during sleep or general anesthesia-induced unconsciousness [27]. The cortical regions may still be receptive to information, but their ability to communicate with other regions may be altered during general anesthesia [28]. According to our knowledge, no study has investigated the way in which the cerebral motor activity was modulated with peripheral nerve stimulation over the sensorimotor cortex during general anesthesia. The aim of this study is to verify that ERD/ERS following MNS is still present and detectable under high doses of propofol with the EEG technique. Such new knowledge will enable the design of an innovative BCI specialized in the detection of intraoperative awareness during general anesthesia.

The first objective of this study is to verify that ERD and ERS patterns induced by MNS can be detected in the cortical motor EEG signal under various concentrations of propofol corresponding to the anesthetic doses required for general anesthesia. The secondary objective is to characterize and understand how the ERD and ERS generated after each MNS will be altered according to each concentration of propofol at the effect site. These results will be discussed in relation to previous results obtained from a protocol investigating the effect of light propofol sedation on EEG signals in the motor cortex. The third objective is to analyze EEG signals offline and try to detect MNS under propofol with new machine learning algorithms. Complementary, the short and middle latency components of the somatosensory evoked potentials (SEPs) will be analyzed for different propofol concentrations. Finally, the long-term goal is to design a BCI that can detect intraoperative awareness during general anesthesia.

Consent collection	N/A^a^	N/A	N/A	N/A
Consent confirmation	N/A	N/A	✓	N/A
Providing information documents	✓	N/A	N/A	N/A
Checking inclusion and exclusion criteria	✓	N/A	✓	N/A
Medical interview	✓	✓	✓	N/A
Clinical examination	✓	✓	✓	✓
Electroencephalographic recording	N/A	N/A	✓	✓
Electromyography recording	N/A	N/A	N/A	✓
Median nerve stimulation	N/A	N/A	✓	✓
Adverse event collection	N/A	N/A	N/A	✓

^a^N/A: not applicable.

^b^d-day: day of experimentation.

Table 1 shows the registration, intervention, and evaluation schedule.

Considering the SEP stimulation, we consider that nonpainful stimuli will consist of square electrical pulses of 0.2 milliseconds of duration, generated by Micromed device Sd Ltm Stim Energy (Micromed) and delivered through a pair of grass gold cup electrodes (cathode [−] placed proximally) to the right/left median nerve at the wrist [32]. The intensity will be adjusted for eliciting visible small thumb twitches and without exceeding 50 mA.

### Study Population

In this clinical protocol, a total of 30 patients who require scheduled surgery under general anesthesia will be enrolled. For the recruitment of this study, we have designed a flyer that will be disseminated through different media channels. Participation in this experiment will not be remunerated. Patients will be exposed to the same risks of general anesthesia limited to propofol. The doses used in this clinical protocol are the same as those that induce loss of consciousness during conventional surgery.

The inclusion criteria include patients (1) who have received full details of the research organization and have signed our informed consent, (2) aged between 18 and 81 years, (3) scheduled for surgery with the use of total intravenous sedation with propofol, and (4) who are affiliated to a social security regime in Belgium. We shall exclude patients who (1) are allergic to propofol or its ingredients, (2) have a history of an anaphylactic reaction during anesthesia, (3) are female due to the impossibility of checking pregnancy status, (4) are deprived of liberty by a judicial or administrative decision, (5) are under psychiatric care, (6) are unable to give consent and without being subjected to a legal protection measure, (7) refuse to participate in the study, (8) have a BMI below 20 or above 35 kg/m², (9) require surgery for less than an hour, (10) have a pathological history related to the right median nerve, and (11) have any drug addiction.

### Ethical Considerations

This research was officially approved by an ethical committee from Belgium (CHU Brugmann, CE 2021/225) and was registered at EUDRACT (2021-006457-56). The study protocol was also registered on ClinicalTrials.gov (NCT05272202). This protocol will follow the principles of the Declaration of Helsinki and the Medical Research Involving Human Subjects Act [33]. Informed written consent will be obtained from all patients before study inclusion. Because involvement of patients is voluntary, the study can be stopped at any time.

### EEG Data Acquisition

Motor EEG signals will be collected through the OpenViBE software platform with eego mylab system (ANT neuro) 64-EEG channels, covering the entire scalp at 16,000 Hz and 1 external channel placed on the dorsum of the contralateral hand to the electric stimulation, by means of an adhesive surface electrode. All offline analyses will be performed using the EEGLAB toolbox [34] and Matlab2016a (The MathWorks Inc). The findings will be additionally investigated by applying a Laplacian filter and a mastoidal re-referencing [35]. Then, the EEG signals will be resampled (128 Hz) and epoched into 6-s windows (1 second before and 5 seconds after the MNS). We will compute the ERD/ERS% using the “band power method” [36]. Additionally, SEP will be calculated by averaging epochs extracted from 0.25 to 0.5 with respect to the electric shock.

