### Statistics

The data processing methods will be similar to those described in the MOTANA protocol [23]. For each patient and each MNS, the maximal value of ERD and ERS max will be, respectively, selected in (0.25;0.5) seconds and (2;4) seconds after stimulation, in accordance with the literature [24,37]. An average over the ERDs max and ERSs max will be performed for each concentration. These 2 values will be, respectively, compared with average ERDs max and ERSs max obtained in the preoperative rest condition with a Student *t* test (*P*<.05). To visualize the event-related spectral perturbations with the EEGLAB toolbox, a surrogate permutation test will be used (*P*<.05; 2000 permutations). In addition to the permutation test, we will apply a false discovery rate correction to show the difference in MNS effect during different concentrations of propofol.

In addition to the event-related spectral perturbation analyses, we will apply 4 different offline machine learning algorithms to detect the MNS at the cerebral level. To do this, these algorithms are based on 4 classification methods in a 4-fold cross-validation scheme. The classification score will be computed for the MNS versus the rest class. Each trial will be segmented into a motor task time window and a resting time window, both lasting 2 seconds. The motor task time window will begin 0.5 seconds after the MNS, and the resting phase time window will begin 3 seconds before the MNS. The first classification method is a linear discriminant analysis method using a common spatial pattern [38] (referred to as common spatial pattern+linear discriminant analysis). For the next 3 classifiers, we will use classifiers that are based on Riemannian geometry. Riemannian geometry-based methods have the advantage of being immune to linear transformations and to be particularly efficient for the detection of motor intentions. For the statistical differences in the latency and topographic voltage of the SEP components, similar permutation tests and post hoc tests will be applied.

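### The SEP epoch as printed starts 250 ms after the shock, so it misses the short- and middle-latency components that the plan says it will analyse

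*Protocol article*

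**What the plan says.** The Introduction adds SEPs to the study's aims as a complementary analysis: "the short and middle latency components of the somatosensory evoked potentials (SEPs) will be analyzed for different propofol concentrations". Statistics then names what will be tested: "For the statistical differences in the latency and topographic voltage of the SEP components, similar permutation tests and post hoc tests will be applied".

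The processing is set out under EEG Data Acquisition. Recording is on 64 channels, "covering the entire scalp at 16,000 Hz". The text continues: "Then, the EEG signals will be resampled (128 Hz) and epoched into 6-s windows (1 second before and 5 seconds after the MNS". Next comes the ERD/ERS percentage by the band power method, and after that the SEP sentence: "Additionally, SEP will be calculated by averaging epochs extracted from 0.25 to 0.5 with respect to the electric shock". The SEP sentence has no unit and no sign, and it gives no sampling rate of its own.

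The same two numbers appear under Statistics for another purpose. There the ERD and ERS maxima are "selected in (0.25;0.5) seconds and (2;4) seconds after stimulation", so 0.25 to 0.5 s is the search window for the ERD peak.

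**The concern.** The aim and the tests concern the early part of the evoked response, while the printed epoch covers a later stretch. An analyst who follows the sentence literally would average 250 ms of signal from +250 to +500 ms and find no short- or middle-latency component whose latency or voltage could be compared across propofol concentrations. With no pre-stimulus segment in the epoch, there would also be no baseline against which to measure voltage.

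A second, conditional worry is the sampling rate. The SEP sentence follows the resampling sentence in the same paragraph. If the SEP average is taken after resampling to 128 Hz, the time grid is coarse relative to early components, and anything above 64 Hz is lost.

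What is at stake is the SEP analysis only. Its stated question, how these components change with propofol concentration, would go unanswered.

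**Working it through.** **Inputs.** From EEG Data Acquisition: SEP epoch 0.25 to 0.5, recording rate 16,000 Hz, resampled rate 128 Hz. From Statistics: ERD peak window 0.25 to 0.5 s. Component latencies are not in the article. I assume short latency at about 15-40 ms and middle latency at about 40-100 ms, with an outer limit of 200 ms. The unit is read as seconds, as in the ERD window.

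**Step 1: does the window contain the components?**

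| Assumed peak (ms) | In +250 to +500 ms (as printed) | In -250 to +500 ms (minus sign restored) |
|---|---|---|
| 20, 30, 45, 60 | none | all |
| 100, 150, 200 | none | all |

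The printed window excludes the whole assumed range. The result would change only if a component counted as middle-latency peaked at 250 ms or later.

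**Step 2: the sampling grid.** Step = 1000/rate (ms). Upper frequency limit = rate/2. Samples in the first 50 ms = 0.05 × rate.

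- At 16,000 Hz: 1000/16,000 = 0.0625 ms; 800 samples in the first 50 ms.
- At 128 Hz: 1000/128 = 7.8125 ms; limit 128/2 = 64 Hz; 0.05 × 128 = 6.4, so about 6 samples in the first 50 ms.
- Ratio of steps: 7.8125/0.0625 = 125.

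**Step 3: what 128 Hz would do to latency and amplitude.** Noise-free Gaussian peaks of height 1 (assumed shapes) were resampled from 16,000 to 128 Hz. The peak was read first from the raw samples and then after band-limited interpolation back to 16,000 Hz.

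| True peak (SD), ms | True shift, ms | Raw peak at 128 Hz, ms | Sampled height | Interpolated peak, ms |
|---|---|---|---|---|
| 20 (2.5) | 0 | 23.44 | 0.51 | 20.12 |
| 20 (2.5) | 2 | 23.44 | 0.652 | 22.25 |
| 20 (2.5) | 5 | 23.44 | 0.646 | 24.75 |
| 20 (2.5) | 10 | 31.25 | 0.66 | 30.19 |
| 45 (7) | 0 | 46.88 | 0.962 | 45.06 |
| 45 (7) | 5 | 46.88 | 0.905 | 50.0 |
| 45 (7) | 10 | 54.69 | 0.994 | 55.0 |
| 100 (15) | 0 | 101.56 | 0.995 | 100.0 |
| 100 (15) | 5 | 101.56 | 0.975 | 105.0 |
| 100 (15) | 10 | 109.38 | 1.0 | 110.0 |

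- *Raw reading.* Shifts of 1, 2 and 5 ms left the raw peak where it was for all three components. A 10 ms shift moved it by one step (for example 31.25 - 23.44 = 7.81 ms). A shift smaller than one step is read either as zero or as a full step, depending on where the peak sits on the grid.
- *Amplitude.* The 20 ms peak is sampled at 0.51 to 0.66 of its true height. A pure 2 ms shift changes the sampled height from 0.51 to 0.652, so a latency change can pass for a voltage change. The two later peaks keep at least 0.905.
- *Interpolated reading.* The 20 ms peak is located to within 25 - 24.75 = 0.25 ms, and its shift to within 5 - (24.75 - 20.12) = 0.37 ms. The later peaks are located to within 0.06 ms. Latency information therefore survives at 128 Hz in this noise-free setting, but the article mentions no interpolation.

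**The case against.** The strongest reply is that the SEP sentence does not say after the shock. Elsewhere, when the authors mean post-stimulus time, they say so. An epoch of -0.25 to 0.5 s would be ordinary, would include a baseline and would contain every assumed peak, so the exclusion may be only a dropped minus sign. That is possible. However, minus signs are intact elsewhere in the text (the visit windows in Table 1 and the cathode polarity in Study Design), so loss in the PDF reading is not the obvious explanation. If the authors made a typing error, the printed parameter is still wrong and needs correcting. The match with the ERD window makes a copied window another possible cause, but shared digits do not prove it.

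The second reply is that no sentence puts the SEPs on the 128 Hz data. The resampling is tied to the 6-s epochs and to ERD/ERS, and the SEP sentence defines its own epoch, which fits a separate branch from the full-rate recording. This stands: the 128 Hz reading is an inference from sentence order. A condensed article may also leave the SEP rate to the full protocol, so its absence is not itself a fault.

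A reader might go further and infer that resampling makes SEP latency differences unmeasurable. The simulation does not support that. Shifts above about 8 ms show even in the raw samples, and interpolation recovers smaller ones. A reader might also take the SEP as the study's check that the shock reached the cortex, so that losing it would undermine the interpretation of an absent ERD. It could serve that purpose, but the article does not give it that role and calls the analysis complementary.

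**Conclusion.** The SEP epoch is wrong as written. Followed literally, it contains none of the assumed component range and no pre-stimulus baseline, in conflict with the aim in the Introduction and the latency tests in Statistics. This rests on reading the numbers as positive seconds and on assumed latencies of about 15-200 ms. Restoring a minus sign would remove the exclusion.

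The sampling-rate part is conditional. If SEPs are taken from the 128 Hz data, short-latency peaks are attenuated (to about 0.51-0.66 of their height in the simulation) and raw peak reading is too coarse for shifts below about 8 ms. Later components are little affected in amplitude.

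The consequence stops at the complementary SEP analysis. SEPs are not named among the primary or secondary end points, and ERD amplitude, the primary end point, does not depend on this epoch.

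**What to change.** - In EEG Data Acquisition, restate the SEP epoch with sign and unit so that it covers a pre-stimulus baseline and the short- and middle-latency range, for example -0.25 to 0.5 s relative to the shock. Check it against the components named in the Introduction and the latency and voltage tests in Statistics.
- State that SEPs are computed in a separate branch from the 16,000 Hz recording, or at a rate well above 128 Hz, and that 128 Hz is used for ERD/ERS only.

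The cost is a few words and some processing time. The plan already records at 16,000 Hz, so no new measurement is needed as long as the raw recordings are kept.
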